## Abstract

**Introduction:**

Atrial fibrillation (AF) is a major public health issue and there is rationale for the early diagnosis of AF before the first complication occurs. Previous AF screening research is limited by low yields of new cases and strokes prevented in the screened populations. For AF screening to be clinically and cost-effective, the efficiency of identification of newly diagnosed AF needs to be improved and the intervention offered may have to extend beyond oral anticoagulation for stroke prophylaxis. Previous prediction models for incident AF have been limited by their data sources and methodologies.

**Methods and analysis:**

We will investigate the application of random forest and multivariable logistic regression to predict incident AF within a 6-month prediction horizon, that is, a time-window consistent with conducting investigation for AF. The Clinical Practice Research Datalink (CPRD)-GOLD dataset will be used for derivation, and the Clalit Health Services (CHS) dataset will be used for international external geographical validation. Analyses will include metrics of prediction performance and clinical utility. We will create Kaplan-Meier plots for individuals identified as higher and lower predicted risk of AF and derive the cumulative incidence rate for non-AF cardio-renal-metabolic diseases and death over the longer term to establish how predicted AF risk is associated with a range of new non-AF disease states.

**Ethics and dissemination:**

Permission for CPRD-GOLD was obtained from CPRD (ref no: 19_076). The CPRD ethical approval committee approved the study. CHS Helsinki committee approval 21-0169 and data usage committee approval 901. The results will be submitted as a research paper for publication to a peer-reviewed journal and presented at peer-reviewed conferences.

**Trial registration number:**

A systematic review to guide the overall project was registered on PROSPERO (registration number CRD42021245093). The study was registered on ClinicalTrials.gov (NCT05837364).

STRENGTHS AND LIMITATIONS OF THIS STUDYLarge and nationwide datasets representative of the community-dwelling populations in two countries.Predicting the risk of incident atrial fibrillation (AF) in the short term may be more useful to screening than longer prediction horizons.Quantification of the strength of association between predicted AF risk and other diseases may uncover other opportunities that could be actioned during AF screening beyond stroke prophylaxis.A calculator created from a parsimonious model may enhance the usability of the model in the real world and in contexts where electronic health records are unavailable or incomplete.It is estimated that more than a quarter of individuals living with AF are not diagnosed during routine care, which may mean that the performance of the prediction model may vary in a screening setting.

## Introduction

Atrial fibrillation (AF) is the most common sustained cardiac arrhythmia. Over the last 20 years, the number of new cases of AF diagnosed each year has risen by 72%, and now surpasses the four most common causes of cancer combined.^1^ Moreover, it is estimated that up to 35% of the disease burden remains undiagnosed,^2^ and 15% of strokes occur in the context of undiagnosed AF.^3^

Oral anticoagulants can reduce the risk of stroke by up to two-thirds in those with AF at higher risk of stroke,^4^ and international guidelines recommend their use in patients with AF at elevated thromboembolic risk.^5^ Early detection of AF may permit the initiation of oral anticoagulation to reduce embolic stroke risk,^4^ and early antiarrhythmic therapy to reduce the risk of death and stroke.^6^ Accordingly, early AF detection is a key cardiovascular priority in the UK National Health Service (NHS) Long Term Plan,^7^ and the European Society of Cardiology recommends opportunistic screening by pulse palpation or ECG rhythm strip in persons aged ≥65 years and systematic ECG screening in those aged ≥75 years.^8^

Furthermore, AF frequently develops due to, and in parallel with, other cardiovascular, renal and metabolic conditions,^9^ and individuals with AF are at an increased risk of major cardiovascular events in excess of stroke including ischaemic heart disease, heart failure, chronic kidney disease, peripheral vascular disease and death.^10^ Thus, AF screening, with or without AF diagnosis, maybe a key opportunity for holistic management of cardiometabolic risk factors and unhealthy lifestyle behaviours to reduce an individual’s risk of later adverse events beyond that of stroke prophylaxis alone.

Several randomised clinical trials (RCTs) have shown that serial or continuous non-invasive ECG monitoring in older people with stroke risk factors/elevated N-terminal pro B-type natriuretic peptide, leads to a higher detection rate of previously undiagnosed AF compared with routine standard of care, though yields remain relatively low (3.0%–4.4%).^11–14^ The STROKESTOP (Systematic ECG Screening for Atrial Fibrillation Among 75 Year Old Subjects in the Region of Stockholm and Halland, Sweden) RCT, where AF screening was offered to individuals aged 75 and 76 years without exclusions, achieved only a 3% yield of new AF cases with a modest benefit in a composite outcome of ischaemic or haemorrhagic stroke, systemic embolism, bleeding leading to hospitalisation and all-cause death; and not for each of ischaemic stroke, haemorrhagic stroke or hospitalisation for major bleeding.^15^ Accordingly, for AF screening to be effective the yield of newly diagnosed AF among participants needs to be improved and the intervention offered may have to extend beyond only oral anticoagulation for stroke prophylaxis (figure 1).

**Figure 1 F1:**
[figure not shown]
A schematic representation comparing current AF screening approaches, which focus on stroke prevention, with a broader approach to AF screening that considers that individuals eligible for AF screening will be at risk of multiple outcomes beyond stroke. AF, atrial fibrillation.

A large proportion of the population is registered in primary care with a routinely collected electronic health record (EHR).^16 17^ A prediction model that uses data available in the community to calculate AF risk could discriminate patients into risk categories, with screening offered only to higher risk individuals,^18^ enabling scalable and efficient targeted AF screening. To date, several multivariable prediction models have been created or tested for the prediction of incident AF in community-based EHRs, but are of limited clinical utility for AF screening on account of moderate discriminative performance, long prediction horizons and limited scalability due to missing data.^19^ None have yet reached widespread clinical practice. Moreover, reports of prediction models have yet to quantify the association between AF risk and new disease states outside that of AF and stroke.

### Research aim

The aims of this study are to:

Develop a model for predicting short-term AF risk from data routinely available in community-based EHRs.Quantify the association of predicted AF risk with a range of non-AF diseases.Externally validate the prediction model in an international context to assess transportability.Produce a calculator derived from a parsimonious prediction model.

## Methods and analysis

### Data sources and permissions

The derivation dataset will be the Clinical Practice Research Datalink-GOLD (CPRD-GOLD) dataset. This is an ongoing primary care database, established in 1987, which comprises anonymised medical records and prescribing data contributed by general practices using Vision software. It contains data for approximately 17.5 million patients, with 30% of contributing practices in England, and represents the UK population in terms of age, sex and ethnicity.^16^ In order to contribute to the database, general practices and other health centres must meet prespecified standards for research-quality data (‘up to standard’).^16 20^

Recorded information includes patients’ demography, clinical symptoms, signs, investigations, diagnoses, prescriptions, referrals, behavioural factors and test results entered by clinicians, and other practice staff. All clinical information is coded using Read Codes.^21^ Extracted patients will have patient-level data linked to Hospital Episode Statistics (HES), Admitted Patient Care (APC) and Office for National Statistics (ONS) Death Registration. The CPRD dataset has been used to develop or validate a range of risk prediction models.^22^

The extracted dataset, including linked data, comprises all patients for the period between 2 January 1998 and 30 November 2018 from the snapshot of CPRD-GOLD in October 2019. Over this study period, the CPRD-GOLD dataset comprises approximately 2 million patients eligible for data linkage at an up-to-standard practice, with over 200 000 patients having a record of AF during follow-up.

To ascertain whether the prediction model is transportable to geographies outside of the UK, we will externally validate its performance in the Clalit Health Services (CHS) database in Israel. As a result of the National Health Insurance Law, Israeli citizens are required to enrol in one of four payer-provider health funds and receive free basic healthcare. CHS provides health insurance coverage to 4.8 million insured members and about two-thirds of the population aged >65 years. CHS is recognised globally as the primary source of evaluation of COVID-19 vaccinations and therapies.^23–26^ All clinical information is coded in International Classifications of Diseases, Ninth Revision (ICD-9). Receipt of vital status from the Ministry of the Interior ensures 100% follow-up of mortality. We will include participants insured by Clalit with continuous membership for at least 1 year before 1 January 2019: 2 159 663 patients with 4330 of them having a new incident of AF (AF and/or atrial flutter (AFl)) in the first half of 2019.

### Patient and public involvement

The Arrhythmia Alliance and AF association provided input on the scientific advisory board for this research programme, and our patient and public involvement group have given input to reporting and dissemination plans of the research.

### Inclusion and exclusion criteria

The study population for derivation and internal validation will comprise all available patients in CPRD-GOLD eligible for data linkage and with at least 1-year follow-up in the period between 2 January 1998 and 30 November 2018. For the external validation, the study population will comprise participants insured by CHS, including those with continuous membership for at least 1 year, before 1 January 2019. Patients will be excluded if they were ≤30 years of age, or diagnosed with AF or AFl at the point of study entry, registered for less than 1 year or, in CPRD, ineligible for data linkage. Patients younger than 30 years of age are not included in the cohort for AF prediction because the incidence of AF over even a 10-year horizon is very low in this group.^1^

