### Prediction model outcome ascertainment

The outcome of interest is first diagnosed AF or AFl after baseline. Baseline is taken in the CPRD-GOLD dataset as the first entry of the patient into the dataset. We have included AFl as an outcome since it has similar clinical relevance, including thromboembolic risk and anticoagulation guidelines, as AF.^5^ These will be identified using Read codes in CPRD dataset. For HES APC events and underlying cause of death variables in the ONS Death Registration data file, ICD-10 codes will be used. For CHS, events will be identified using ICD-9 codes. It should be noted that a report has estimated that 305 262 individuals in the UK have undiagnosed AF,^27^ and so incidence of AF within the study may be underestimated as there will be individuals with unrecorded asymptomatic AF.

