**Figure 2 F2:**
[figure not shown]
A schematic representation of a multivariable logistic regression model or random forest model using data from electronic health records to provide risk prediction for incident AF. AF, atrial fibrillation.

Preprocessed patient-level data in CPRD-GOLD will be randomly split into an 80:20 ratio to create derivation and internal validation (or training and testing) samples. The split ratio is not a significant factor, given the volume of the sample size. The model parameters and drop-out rate will be chosen through a grid search and 10-fold cross-validation will be used (ie, 10% of the training data will be randomly selected as the cross-validation set). The multivariable logistic regression model will be developed with backward model selection with Akaike information criterion.^37^ The prediction window will be set at 6 months, as this is considered in keeping with the logistical time frames for organising AF investigation at scale.

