We will create Kaplan-Meier plots for individuals identified as higher and lower predicted risk of AF to assess the event rate for non-AF outcomes censored at 10 years. We will derive the cumulative incidence rate for each outcome at 1, 5 and 10 years considering the competing risk of death, as well as death at 5 and 10 years. For each specified outcome, we will calculate the HR between higher and lower predicted risk of AF using Fine and Gray’s model with adjustment for the competing risk of death. We will also report adjusted HR where the model is adjusted for age, sex, ethnicity and the presence of any of the other outcomes at baseline. As some of the outcomes have incidence rates that are strongly associated with age (eg, aortic stenosis) or differ by sex (eg, heart failure),^39 40^ we will conduct subgroup analyses of incidence rates for higher and lower risk individuals for each outcome by age group (30–64 years and ≥65 years) and sex. As some of the non-AF outcomes are more likely to occur in the setting of prevalent AF (eg, stroke or heart failure),^9^ we will also conduct a sensitivity analysis whereby people with incident AF during follow-up are excluded.

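### As written, CPRD eligibility requires a year of follow-up after the moment of prediction, twice the 6-month horizon; the eligibility and baseline definitions must be reconciled

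*Protocol article*

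**What the plan says.** Four statements in the protocol article bear on this point.

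- **Inclusion and exclusion criteria, CPRD.** Patients enter derivation and internal validation if they are eligible for linkage and "with at least 1-year follow-up in the period between 2 January 1998 and 30 November 2018". The exclusion list then removes those "registered for less than 1 year or, in CPRD, ineligible for data linkage", without saying from which date the year is counted.
- **Inclusion and exclusion criteria, CHS.** The external cohort is insured members, "including those with continuous membership for at least 1 year, before 1 January 2019". No requirement after that date is stated.
- **Prediction model outcome ascertainment.** "Baseline is taken in the CPRD-GOLD dataset as the first entry of the patient into the dataset". "The outcome of interest is first diagnosed AF or AFl after baseline". On the linked sources: "For HES APC events and underlying cause of death variables in the ONS Death Registration data file, ICD-10 codes will be used".
- **Prediction model development.** "The prediction window will be set at 6 months".

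The section on long-term AF and other diseases uses the CPRD testing set, so it inherits the CPRD eligibility rule. It reports cumulative incidence "at 1, 5 and 10 years considering the competing risk of death, as well as death at 5 and 10 years".

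**The concern.** Follow-up from first entry runs forward in time. If a year of it is an entry condition, membership of the derivation cohort depends on what happens after the prediction is made. A clinician using the model cannot know who will still be alive and registered in 12 months, so the estimated risk would belong to a population that cannot be identified when the model is applied.

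Absolute risk matters in this study. The Internal validation section plans calibration, the Brier score, decision curves, and reclassification at a threshold set to the cohort's mean 6-month incidence. Internal validation cannot expose the problem, because the 20% testing split carries the same selection. External validation might, but CHS is selected on the past and CPRD, read literally, on the future. Miscalibration in CHS could then partly reflect that difference and be read as poor transportability, which is one of the study's stated aims.

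**Working it through.** **1. Timeline on the literal reading.** Baseline is first entry (month 0), the outcome window is months 0 to 6, and eligibility requires follow-up to month 12. A person diagnosed with AF in month 3 who dies in month 9 has the model outcome but is not in the cohort. A person whose AF is first recorded at death in month 4 is not in it either, so AF first recorded at death within the window cannot be a model outcome.

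**2. One-year results.** If everyone in the testing set survives 12 months, no deaths compete with the 1-year cumulative incidences.

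**3. CPRD against CHS.** CPRD requires a year after time zero. CHS requires a year before 1 January 2019 and counts AF in the first half of 2019. The two cohorts are selected differently.

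**4. The plan's own figure.** The Sample size section uses 200 parameters, Cox-Snell R² of 0.01 and shrinkage of 0.95: 200 / [(0.95 − 1) × ln(1 − 0.01/0.95)] = 377 996.5, against 377 996 stated. It reproduces and does not depend on the eligibility rule.

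**5. Size of the selection effect.** Let r be the true 6-month AF risk, and let m1 and m0 be the probabilities of dying within a year of entry with and without AF in the window. Counting deaths only, the risk in the retained cohort is

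q = r(1 − m1) / [r(1 − m1) + (1 − r)(1 − m0)].

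Inputs: r = 4330 / 2 159 663 = 0.2005%, from the CHS figures under Data sources and permissions, used as a stand-in for CPRD. The article gives no mortality figures, so m1 and m0 are assumptions.

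Example with m1 = 20% and m0 = 1%: the numerator is 0.002005 × 0.80 = 0.001604; the denominator is 0.001604 + 0.997995 × 0.99 = 0.989619; q = 0.1621%; q/r = 0.808.

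| m1 (assumed) | q/r, m0 = 0.5% | q/r, m0 = 1% | q/r, m0 = 2% |
|---|---|---|---|
| equal to m0 | 1.000 | 1.000 | 1.000 |
| 5% | 0.955 | 0.960 | 0.969 |
| 10% | 0.905 | 0.909 | 0.919 |
| 20% | 0.804 | 0.808 | 0.817 |
| 30% | 0.704 | 0.707 | 0.715 |

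Because r is small, the ratio is close to (1 − m1)/(1 − m0) and hardly depends on r. The share of AF cases lost equals m1: per 4330 cases, from 4330 × 0.05 = 216.5 to 4330 × 0.30 = 1299.

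**The case against.** The strongest reply is that the year was meant as look-back. The exclusion of people registered for less than a year stands in a list that includes a condition judged at study entry, and it covers both databases. Read as look-back, it matches CHS. Predictor diagnoses are taken from the record with no time limit, which presupposes history before entry. CPRD dates from 1987 and the extract from 1998, so many patients could have earlier registration. Applying death as a competing event at 1 year also suggests that first-year deaths were expected.

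This stands as a plausible account of intent, but it does not rescue the text. A look-back year is not follow-up, and it does not fit a baseline at first entry unless entry is defined as the completion of that year, which the article does not say. Two analysts could extract different cohorts from these sentences.

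It is also fair to say that a binary 6-month classifier needs some rule for incomplete follow-up. That would justify a condition at 6 months at most, not at 12.

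Four stronger inferences are tempting and are not supported:

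- **Death is listed only at 5 and 10 years, so the first year must be free of death by design.** These are reporting times; nothing ties them to the eligibility rule.
- **The death-registration source contradicts the criterion.** It still serves the 10-year AF analysis. Only its contribution within the 6-month window disappears.
- **People who leave a practice in year 1 add to the under-estimate.** That depends on how leaving relates to AF, on which the article is silent.
- **The bias is at least about 9%.** That floor appears only if mortality after new AF is assumed to be 10% or more. At 5% the loss is 3–5%.

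**Conclusion.** The point holds, conditional on the reading. As written, CPRD derivation and internal validation are restricted to people alive and registered 12 months after prediction, while CHS is not. If a look-back year was intended, the criterion and the baseline definition are both misworded. On either reading the two sections cannot both stand unchanged.

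The likely direction is under-prediction, provided one-year mortality is higher after new AF than without it. The size cannot be computed from the article. Under assumed one-year mortality of 5–30% after new AF and 0.5–2% otherwise, retained risk is about 0.97 to 0.70 of true risk; equal mortality gives a ratio of 1. The effect on individual coefficients has not been quantified, and the stated sample size is unaffected.

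**What to change.** Before extraction, amend the CPRD rule as follows.

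1. Replace the follow-up condition with at least 1 year of up-to-standard registration before the index date, as in CHS.
2. Redefine CPRD baseline as the latest of study start, completion of that year, and the date on which the age criterion is met. Changing the eligibility wording alone would leave the clash with baseline at first entry.
3. Require no survival or retention after baseline.
4. Count AF within 6 months as an event, including AF first recorded at death; count death without AF as a non-event.
5. Exclude only people whose index date falls less than 6 months before the end of the data (30 November 2018). Handle transfer-out before 6 months with inverse-probability-of-censoring weights.
6. Start follow-up for long-term AF and the other diseases at the same index date.

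The cost is a change to the extraction rule and wording, with no new data. One year of registration per patient is spent as look-back, and a small share of records needs weighting.

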### Prediction model outcome ascertainment

The outcome of interest is first diagnosed AF or AFl after baseline. Baseline is taken in the CPRD-GOLD dataset as the first entry of the patient into the dataset. We have included AFl as an outcome since it has similar clinical relevance, including thromboembolic risk and anticoagulation guidelines, as AF.^5^ These will be identified using Read codes in CPRD dataset. For HES APC events and underlying cause of death variables in the ONS Death Registration data file, ICD-10 codes will be used. For CHS, events will be identified using ICD-9 codes. It should be noted that a report has estimated that 305 262 individuals in the UK have undiagnosed AF,^27^ and so incidence of AF within the study may be underestimated as there will be individuals with unrecorded asymptomatic AF.

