For non-AF disease states, we will consider the initial presentation of a cardiovascular, renal or metabolic disease or death. This is because AF is not a disease in isolation and is known to be associated with a high risk of adverse clinical outcomes. To best characterise highly prevalent and morbid diseases, associated with the development or consequence of AF and that may be appropriate for prevention or targeted diagnostic pathways subsequent to AF screening (online supplemental figure 1),^9^ we will individually examine the following nine conditions: heart failure, valvular heart disease (and specifically aortic stenosis), myocardial infarction, stroke (ischaemic and haemorrhagic) or transient ischaemic attack, peripheral vascular disease, chronic kidney disease, diabetes mellitus and chronic obstructive pulmonary disease. These disease states have been further selected for investigation because interventions could be implemented and/or tested to reduce their clinical progression. We will also quantify the occurrence of death by any cause recorded in primary care or by death certification from the UK Death Register of the ONS, which will be mapped on to nine disease categories (online supplemental table 2). For each condition, a list of diagnostic codes from the CALIBER code repository, including from ICD-10th revision (used in secondary care) and Read coding schemes (used in primary care) will be defined comprehensively to identify diagnoses from EHRs. Incident diagnoses will be defined as the first record of that condition in primary or secondary care records from any diagnostic position. For the definition of new cases, we will exclude individuals for the analysis of each condition who had a diagnosis of that condition before the patient’s entry to the study. If no indication of a specific disease is recorded, then the patient will be assumed to be free from the disease. CPRD is a positive recording dataset, which reduces the likelihood of the non-recording of a clinically identified disease state.

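### CPRD baseline is the first entry, with no guaranteed earlier record, while CHS patients have at least a year; AF and predictors recorded late in new registrants could distort the 6-month outcome

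*Protocol article*

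**What the plan says.** The outcome section of the protocol article fixes time zero for CPRD: "Baseline is taken in the CPRD-GOLD dataset as the first entry of the patient into the dataset". The section on long-term AF and other diseases treats baseline and study entry as the same point. The outcome is defined relative to it: "The outcome of interest is first diagnosed AF or AFl after baseline". Under Prediction model development, "The prediction window will be set at 6 months".

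Inclusion and exclusion criteria contains two 1-year conditions that bear on CPRD. The population consists of linkable patients "with at least 1-year follow-up in the period between 2 January 1998 and 30 November 2018", and patients are excluded if "registered for less than 1 year or, in CPRD, ineligible for data linkage". The second condition gives no date from which the year is counted. Patients with AF or flutter already diagnosed at study entry are also excluded.

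For CHS the year is anchored: "We will include participants insured by Clalit with continuous membership for at least 1 year before 1 January 2019".

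Under Predictor variables, a diagnosis counts as present if a code exists at any earlier time, and as absent if no code is found. For the non-AF conditions, "we will exclude individuals for the analysis of each condition who had a diagnosis of that condition before" study entry.

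**The concern.** Reading a missing code as no disease is reasonable only if the record has had time to accumulate. For a patient who joins a practice during the study period, first entry may be the start of the record, and the whole 6-month window then falls in its earliest part. AF that existed before entry but was recorded only afterwards would meet the outcome definition. Comorbidities recorded in the same period would be entered as absent predictors.

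The intercept and coefficients would then partly describe record-building rather than new disease, and would suit established primary care records less well. Internal validation would not reveal this, because the 20% test set uses the same time zero. The net reclassification threshold would move too, since it is set at the cohort's average 6-month incidence. In CHS, poor calibration could be put down to geography when the look-back also differs. The 1-year cumulative incidences of the non-AF conditions are exposed in the same way. The article's only caveat on AF recording points the other way, towards under-ascertainment.

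**Working it through.** **Step 1: the passages side by side.**

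- CPRD time zero: first entry, which is also study entry.
- CPRD 1-year conditions: one is worded as follow-up inside the study period, the other as length of registration with no anchor.
- CHS 1-year condition: "continuous membership for at least 1 year before 1 January 2019", so it precedes the index date.

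The unanchored registration year can be read in two ways.

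1. It counts total registration, or time after baseline. Then CPRD has no minimum look-back. If it is time after baseline, eligibility also depends on what happens after time zero.
2. It must be complete before study entry. Then the look-back exists, but for anyone registering within the study period baseline is no longer the first entry, unless that phrase means entry to the study cohort.

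Either reading requires a change of wording. Under the first, the 6-month outcome has the problem described.

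**Step 2: inputs.**

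- Prevalence P = 1.7% (Sample size; a figure for England).
- 6-month incidence I = 4330 / 2 159 663 = 0.2005% (Data sources and permissions; CHS, first half of 2019).
- f = share of prevalent AF first coded in the 6 months after entry. Not in the document; assumed.
- w = share of the cohort that is newly registered. Not in the document; assumed.

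P / I = 0.017 / 0.002005 = 8.5. Prevalent cases outnumber 6-month incident cases more than eightfold, so a small late-coded fraction matters.

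The article's required sample size reproduces: 200 / ((0.95 − 1) × ln(1 − 0.01/0.95)) = 377 996.5, against 377 996 stated. It does not depend on time zero and so does not test this point.

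**Step 3: share of apparent 6-month cases that are really prevalent.**

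Share = w·f·P / (w·f·P + I); inflation of apparent incidence = 1 + w·f·P / I.

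| w | f | w·f·P | Share | Inflation |
|---|---|---|---|---|
| 100% | 2% | 0.00034 | 14% | 1.17 |
| 100% | 5% | 0.00085 | 30% | 1.42 |
| 100% | 10% | 0.00170 | 46% | 1.85 |
| 30% | 2% | 0.000102 | 5% | 1.05 |
| 30% | 5% | 0.000255 | 11% | 1.13 |
| 30% | 10% | 0.000510 | 20% | 1.25 |

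With w = 100%, half of the apparent cases would be prevalent at f = 0.002005 / 0.017 = 11.8%.

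**The case against.** The case on the other side has real weight.

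- **Recorded AF is excluded.** A reader might infer that prevalent AF enters the cohort freely. It does not: AF or flutter diagnosed by study entry is an exclusion, so only AF unrecorded at that point can leak in. Linked hospital data might also identify some earlier AF, although the criteria do not say that they will be used for this.
- **The two sections need not contradict each other.** A reader might infer that the registration year is impossible to satisfy at first entry. That holds only if first entry means the registration date and the year must precede it. The text is ambiguous, not self-defeating.
- **Look-back is not absent.** Any earlier code counts, without a time limit, and patients registered well before 2 January 1998 may have long records. What is missing is a guaranteed minimum.
- **Late coding is not documented.** Nothing in the article says how quickly a new patient's history is recorded. The mechanism is plausible, but f is an assumption, and P and I come from different countries.
- **CHS offers a partial check.** Over-prediction would tend to show in the CHS calibration plots, though its cause could not be separated from geography.

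It can also be said that index-date detail belongs in a fuller document. That does not answer the point, because the article does fix time zero, and the rule it fixes carries no minimum history.

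**Conclusion.** The point stands in a limited form. As written, CPRD patients have no guaranteed record before baseline and CHS patients have at least a year. For those registering during the study period, AF unrecorded at entry could be counted as incident, and uncoded predictors or prior conditions would be taken as absent. The external validation would then compare cohorts that differ in look-back as well as in country.

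The size cannot be established from the document. The 14%, 30% and 46% figures rest on proxy rates, on assumed late coding of 2%, 5% and 10%, and on applying that to the whole cohort. With an assumed 30% of new registrants they fall to about 5%, 11% and 20%. A reader might take 46% as an estimate of the bias; the document does not support that. The figures show only that the 6-month outcome is sensitive to small amounts of late recording.

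**What to change.** Reconcile the inclusion criteria with the baseline definition by giving CPRD an explicit index date: the latest of 2 January 1998, the practice's up-to-standard date, registration plus one year, and the date of reaching the minimum age. Then:

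- take predictors and prior disease only from records up to that date;
- exclude anyone with AF or flutter recorded in Read or HES data up to that date;
- start the 6-month window and the follow-up for the non-AF conditions there.

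This gives CPRD the same minimum history as CHS. It does not reproduce the CHS design, which uses one calendar date for everyone, so a difference in calendar time remains and should be acknowledged. If the sponsor already intends a year of registration before baseline, rewording the baseline sentence and anchoring the registration year will settle it. A sensitivity analysis excluding AF first coded soon after registration would show how much late recording matters.

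The cost is a revised definition and its code, plus the first year of follow-up for newly registered patients. The article describes a dataset of approximately 2 million patients, so the loss should be affordable, but the share newly registered is not given.
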